### Eligibility and recruitment

Participation in RADAR is dictated by the Health Director and leadership within each First Nations community health facility. After agreeing to participate, local healthcare workers (e.g., Health Center, Healing Center) will actively register First Nations patients with diabetes into the CARE platform. All patients in the community are eligible to be included in the CARE platform; however, patients must meet the following criteria to be evaluated within RADAR:
*Inclusion criteria*: Patients diagnosed with type-2 diabetes; recently (within last 1-2 years) received care from the First Nations health facility; provided verbal consent for First Nations health care workers to manage their diabetes.
*Exclusion criteria*: Patients with type-1 diabetes; patients <18 years of age; those who are subsequently discovered not to have type-2 diabetes; those refusing care within the First Nations health facility; patients with type-2 diabetes identified after the conclusion of the baseline phase of the project.

### Implementation and evaluation

The implementation and evaluation of RADAR is segregated into two distinct parts. OKAKI Health Intelligence Inc., who has a long history of working with First Nations communities in the province, will implement RADAR, including the CARE platform and care coordination. Researchers from the University of Alberta will independently evaluate the effectiveness of RADAR. By separating the implementation from the evaluation, we believe a more robust evaluation will be achieved. To ensure a robust evaluation, a modified stepped wedge controlled implementation trial design will be employed. This design is a highly valid cross-over design, whereby each community serves as its own control before ‘switching’ to the intervention at different time points [23, 24]. In essence, RADAR will be implemented sequentially to the communities in consecutive 4–6 month periods, based on the communities ‘readiness’. By the end of the evaluation period, RADAR will have been implemented in all communities (Fig. 1).

**Fig. 1 Fig1:**
[figure not shown]
RADAR Stepped-Wedge Design

### Implementation design

#### Baseline ‘control’ phase

Once a community has been allocated to begin RADAR, the community will enter into an initial 6-month prospective baseline phase. During the baseline phase, the CC will work with the local healthcare workers to recognize all known patients with diabetes through existing medical records and histories, ad-hoc registries, etc. All newly identified patients with type-2 diabetes discovered during the baseline phase will also be included. Once identified, all patients will be registered into the CARE platform, including their demographic and clinical data (e.g., A1c, blood pressure, lipids, eye exams, foot care), where available. Patient information to populate the baseline data will be obtained from all potential sources (e.g., medical records, patient interviews, Alberta’s provincial EHR for laboratory results (Netcare)). All available data up to 18 months prior to the end of the baseline period will be used to populate the CARE platform, as patient encounters with the health system may not be consistent. Patients identified with type-2 diabetes following the conclusion of the baseline phase will be included in the CARE platform and process of care coordination but will not be included in analyses, as no baseline control phase will be available for these patients. Importantly, although the CC will work with the local healthcare workers to recognize and register patients with type-2 diabetes, the CC will not make care management recommendations during the baseline phase.

### Intervention phase

After completion of the *Baseline Phase*, each community will transition into the *intervention phase* for a minimum of 1 year. The intervention phase will conclude on December 31, 2020, for all communities and length of follow-up is dependent on timing of initiation of RADAR within the community. During the intervention phase, the CC will help the local healthcare workers to proactively manage patients with type-2 diabetes, including monitoring and recall of patients, relaying clinical information and coordinating care, facilitated through shared use of the CARE platform and web conferencing technologies. In addition, the CC will provide support on the use of the CARE platform and training and education for the local healthcare workers on ‘best practices’ for the management of type-2 diabetes. It is expected that the local healthcare workers’ reliance on the CC will diminish over time, as they become more confident and competent using the CARE platform and in their diabetes knowledge and ability to manage patients, leading to sustainability.

### Evaluation design

We will conduct a comprehensive evaluation of RADAR, using the RE-AIM framework [25]. We have used this framework to evaluate other diabetes-related, quality-improvement interventions [26]. RE-AIM consists of five dimensions: **R**each into the target population; **E**ffectiveness of the intervention; **A**doption by targeted end-users; **I**mplementation, including consistency and cost of delivery; and **M**aintenance of intervention effects over time [25] Table 1.

Thus, our comprehensive evaluation will include both quantitative and qualitative components. We will use the quantitative data for the clinical outcomes mentioned above as part of our overall assessment of the dimension of effectiveness. The primary source of qualitative data includes interviews during the baseline, intervention and post intervention phases. We will use purposeful sampling to identify key informants with expert knowledge of the implementation of RADAR in each community (e.g. the CC, local healthcare workers, and health directors). All interviews will take place at community health facilities or via videoconferencing, using semi-structured interview guides. The purpose of the interviews is to document the organization of existing type-2 diabetes care within each community, implementation facilitators, barriers, and lessons learned, perceived appropriateness of RADAR for the communities, and the overall usability and acceptance of the technology (i.e., CARE platform). In addition, the software vender will also capture changes made to the software over time as requested by the communities. The interviews will be digitally recorded for subsequent analysis, transcribed verbatim by an independent transcriptionist, and verified for accuracy. All qualitative data sources (e.g. validated baseline assessments and interview transcripts) will be compiled and managed using Atlas.ti 7 software.

### Data analysis

For quantitative data, all relative changes will be analyzed using the last known recorded value from the CARE platform from baseline to the end of the intervention phase. We will employ an intention-to-treat analysis, whereby all patients who are enrolled and have baseline data will be included in our primary analysis. The primary endpoint (i.e., 10% improvement in any of A1c, BP, cholesterol values from baseline or those maintaining values within 10% of baseline if at any or all three targets at baseline) will be evaluated using a conventional intention to treat analysis with logistic regression. However, if the observed intracluster correlation coefficient (ICC) is non-ignorable, we will use generalized estimating equations (GEE) that accounts for the clustered and hierarchical nature of our data [24]. Several a-priori subgroup analyses are planned for the primary endpoint. First, we will restrict analyses to patients not at target for any of the 3 primary outcome measures. Second, we will restrict analyses to those patients who were at target for each primary outcome measure (A1c, BP, cholesterol) to fully examine persistence at target over time. Additional subgroups of interest include analyses stratified by sex, and analyses stratified by age (<65 vs > =65 years). Secondary endpoints include: the proportion of clinical measures completed in accordance with guidelines (e.g., A1c, BP, cholesterol, foot and eye examination, receipt of vaccinations, smoking cessation counseling); the number of patients registered in CARE; and the proportion of patients linked to a health services provider.

We anticipate not having complete quantitative data on all endpoints of interest, given the real-world implementation of the project. Several approaches will be used for missing clinical data. First, in alignment with the intention-to-treat approach, we will use the baseline observation carried forward technique for our primary outcome. The stability of the results will be additionally evaluated using the multiple imputation method as a sensitivity analysis.

For qualitative data analysis, we will use an integrated approach. First, we will use the RE-AIM framework as the initial coding structure. Second, we will use an inductive approach [27] to identify emerging codes and concepts within each dimension using conventional approaches [28–30]. We will employ several verification strategies to ensure the reliability and validity of the qualitative results including methodological coherence, appropriate sampling, collecting and analyzing data concurrently [31], and debriefing [30].

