### Power and sample size

In prior studies, about 40% of diabetes patients will have at least a 10% improvement in A1c, BP, and cholesterol over time when studied under ‘usual care’[32]. To detect at least an additional 10% improvement in the proportion of patients achieving our primary endpoint under the RADAR model (i.e., move the population from 40% achieving endpoint to at least 50% achieving endpoint), at an alpha =0.05, an ICC of 0.01, we require 1153 total patients to detect a clinically important difference with 80% power. Assuming a 10% loss to follow-up, we require approximately 1250 total patients among our communities.

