## Discussion

It is well known that diabetes care is suboptimal in First Nations populations [4–6]. Our own research [20, 32], coupled with other large-scale research projects across the country, has clearly demonstrated the need for improved care in this high-risk population [5, 6]. We will evaluate the effectiveness of RADAR in improving the quality of care for First Nations people with type-2 diabetes living on reserve. The aim of RADAR is to improve processes of care, and ultimately clinical outcomes in patients, and to build local capacity and expertise in the management of diabetes. The current Canadian Diabetes Association Clinical Practice Guidelines strongly advocate for multidisciplinary teams to improve outcomes in people with diabetes [8], yet these multidisciplinary teams are often lacking in First Nations communities [5]. We believe RADAR, including the CARE platform and CC model, can facilitate a culturally relevant community-based multidisciplinary team approach to diabetes care.

There are several strengths related to our implementation and evaluation of RADAR. First, the RADAR model is well positioned to succeed in the communities based on prior work by our team. OKAKI Health Intelligence Inc. has been successfully working in First Nations communities in the province for over 7 years. This partnership reinforces that RADAR is community-specific, culturally relevant and promotes its sustainability. Moreover, the communities have already adopted the CARE platform for other aspects of patient care (e.g., home care). Therefore, the extension of the CARE platform to chronic disease management is highly feasible.

Second, our use of the RE-AIM framework will provide insight into the broader impact of RADAR beyond clinical effectiveness and identify both facilitators and barriers to implementing RADAR within each community. These results will help inform scale and spread of RADAR to other suitable communities and populations.

Third, we will employ a valid stepped wedge study design. Often quality-improvement projects show benefit when evaluated, but are conducted without a robust comparison group, making assessment of the true absolute improvements in care difficult to decipher. By including control periods over time, we will be able to elucidate any improvements directly attributed to the RADAR model.

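### The primary endpoint is defined only as change from baseline to a value taken after the switch to RADAR, so the planned analysis contains no control response and cannot estimate the RADAR effect that the article claims

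*Protocol article*

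**What the plan says.** All references are to the protocol article.

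- **Endpoint (Outcomes; Data analysis).** Success is a 10% improvement in any one of A1c, BP or cholesterol, or staying within 10% of baseline for patients already at target. On the values used: "relative changes will be analyzed using the last known recorded value from the CARE platform from baseline to the end of the intervention phase". Missing outcomes take the baseline observation. The model is logistic regression, or GEE if the intracluster correlation is not negligible.
- **Control phase (Baseline 'control' phase).** Each community has a 6-month prospective baseline phase. Records reaching back 18 months from its end may populate the patient's baseline data. No change or response within this phase is defined.
- **Timing (Intervention phase; Implementation and evaluation).** Every community spends at least a year on RADAR. "The intervention phase will conclude on December 31, 2020, for all communities", and "By the end of the evaluation period, RADAR will have been implemented in all communities".
- **Sample size (Power and sample size).** The planning rate comes from prior studies: "about 40% of diabetes patients will have at least a 10% improvement in A1c, BP, and cholesterol over time when studied under" usual care. The aim is to "move the population from 40% achieving endpoint to at least 50% achieving endpoint".
- **Claim (Discussion).** "By including control periods over time, we will be able to elucidate any improvements directly attributed to the RADAR model".

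**The concern.** A stepped wedge identifies an intervention effect by comparing outcomes measured under control with outcomes measured under intervention, with calendar time accounted for. Here the control phase gives a reference value but no outcome. Staggered switch dates then alter only how long each patient is followed on RADAR.

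The result would be a before-after change presented as a controlled effect. Changes in prescribing, testing or population health over calendar time, regression to the mean, and ordinary within-person variation would all contribute to the success proportion, and the planned analysis could not separate them from RADAR. The last matters particularly for an endpoint met by a 10% change in any one of three noisy measures.

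**Working it through.** **1. Is there a contrast?** For each patient the endpoint has three parts:

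- starting value: the last value by the end of the baseline phase;
- follow-up value: the last recorded value by the end of the intervention phase, after the patient's own community switched;
- if there is no follow-up value: baseline carried forward.

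No row in this data set is a response over a control interval. An indicator for RADAR equals 1 in every row and is collinear with the intercept. The model estimates P(success), not a difference or odds ratio for RADAR. Adding covariates or a GEE working correlation does not change that.

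**2. What was the sample size built for?** Inputs from Power and sample size: 40% versus 50%, alpha 0.05, power 80%, ICC 0.01, total 1153. Two-sided testing is assumed, as sidedness is not stated.

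- Two-proportion formula, per group: n = [1.960·√(2·0.45·0.55) + 0.842·√(0.4·0.6 + 0.5·0.5)]² / 0.10² = 387.3, so 388 per group and 776 in total.
- Implied design effect: 1153/776 = 1.486. From 1 + (m − 1)·0.01 = 1.486, m is about 50 patients per cluster. Cluster size and number of communities are not given, so 1153 can be neither confirmed nor refuted.
- One proportion against a fixed 40%: n = [1.960·√0.24 + 0.842·√0.25]² / 0.10² = 190.7, about 191 before clustering.

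The stated total is compatible with a two-condition comparison. The endpoint as defined supplies only one of the two conditions.

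**3. How much could non-RADAR sources contribute? (illustration only)** The documents give no within-person coefficients of variation (CVs), so these are assumed. Errors are taken as normal, independent between measures and between the two time points. With a shared proportional drift s, a measure falls by at least 10% with probability

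p = Φ{ [0.9 − (1 − s)] / [CV·√((1 − s)² + 0.81)] }

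and P(any of three) = 1 − Π(1 − p). Worked example for CVs of 3%, 5% and 7% and s = 0: p = 0.7%, 6.9% and 14.4%, so 1 − 0.993 × 0.931 × 0.856 gives about 21%.

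| Assumed CV: A1c / BP / cholesterol | No drift | 1% drift in all three | 2% drift in all three |
|---|---|---|---|
| 3 / 5 / 7% | 21% | 25% | 30% |
| 4 / 7 / 9% | 34% | 39% | 44% |
| 5 / 8 / 10% | 41% | 45% | 50% |

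Before rounding, the increments are 4.4 to 4.7 points for 1% and 9.4 to 9.7 points for 2%. A 2% drift in only one measure adds about 1 to 5 points. A wider CV range moves the no-drift figure from 10% (CVs 3/4/5%) to 54% (8/10/12%). Persistence at target, which adds successes, and baseline carry-forward are not simulated. Nor is regression to the mean from selected high baselines.

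**The case against.** **The control comparison may sit in a document not shown.** The Outcomes section speaks of improvement over baseline control periods, Implementation and evaluation says each community is its own control, and the sample size fits two conditions. An article may leave model terms to an analysis plan, and Figure 1 is not visible. It stands that a two-condition contrast was probably intended. However, the article does fix the endpoint, and the baseline control period appears in it only as the reference value. An analysis plan can add time terms, but it cannot recover a RADAR effect from an endpoint on which exposure never varies. The endpoint rule itself has to change.

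**Limits are partly disclosed.** The article calls the design modified and non-random, and describes it as a controlled before-after study with sequential roll-out. That concerns allocation. It does not supply a control response, and the Discussion still claims attribution.

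A reader might also infer three stronger points that the documents do not support:

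- *Every score is taken when all communities are on RADAR.* A last known value can predate full roll-out, and carried-forward scores contain no value measured under RADAR. What holds is narrower: no score is a control-interval response.
- *The result will be tested against 40%.* No section says so; 40% is a planning rate. It would also be a weak yardstick, because as described it does not mention persistence at target, which counts as success here.
- *Drift alone would equal the whole 10-point effect.* That needs the assumed CVs and a favourable 2% shift in all three measures together. At 1% the rise is about half that.

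**Conclusion.** The point holds. As the endpoint is defined, the primary analysis yields a success proportion after the switch to RADAR. It yields no RADAR effect, and it does not support the Discussion's attribution statement or deliver the 40% versus 50% comparison. This conclusion follows from the text and needs no numerical assumption.

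The size of the possible distortion does depend on assumptions. Under the central CV ranges (A1c 3–5%, BP 5–8%, cholesterol 7–10%), 21% to 41% of patients succeed by chance alone, and a shared drift of 1% to 2% adds about 4 to 10 points, against a target difference of 10 points. These figures illustrate scale; they are not an estimate of bias in this trial. Because the trial's main causal conclusion rests on this contrast, the point should be settled before analysis.

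**What to change.** 1. **Make the RADAR effect estimable.** Use the dated values in CARE (18-month look-back, baseline phase and intervention phase). Model repeated A1c, BP and cholesterol with RADAR status, fixed calendar period, and community and patient correlation.
2. **Score the binary endpoint in both conditions.** Where values allow, apply the same rule over control and intervention intervals of equal length, and analyse with the same terms.
3. **Keep the existing endpoint** of change to the end of the study as a descriptive before-after result, and state that 40% is a planning rate and not the comparator.
4. **Recheck power** for the new contrast. No replacement sample size can be given here, because the article does not state the number of communities or the period sizes.
5. **If the data cannot support this,** describe the primary analysis as an uncontrolled before-after comparison and remove the attribution statement from the Discussion.

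**Cost.** Revised analysis text, more programming and a new power calculation, with no new data collection foreseen. The real downside is sparse control-interval data. The article itself says that encounters may be inconsistent and data incomplete, so some patients will lack two suitably spaced control values. Precision will be lower than the stated power suggests, and part of the control interval will rest on records that predate the prospective baseline phase.

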### Setting

RADAR involves collaboration with several First Nations communities in Alberta, representing separate treaty areas across the province (continuous expansion of the RADAR model to additional First Nations communities is ongoing). We estimate that approximately 1000 people with type-2 diabetes currently reside in the pilot communities. All communities involved are several hours of travel from a major urban center, where the majority of diabetes specialist care services are located. Some communities have local family physician clinics, located just off reserve that also provide care for patients with diabetes; other communities have visiting family physicians on one or more days a week; while other communities have no local physician services, although services are available in neighboring rural communities. As a result, local, on-reserve, healthcare workers are the primary service providers delivering diabetes care and general health services for these populations. Prior to implementing RADAR, all communities were familiar with the CARE platform for the management of patient care within their respective communities.

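### The primary analysis accounts for community clustering only if the observed ICC looks non-ignorable, although the trial is sized for an ICC of 0.01

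*Protocol article*

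**What the plan says.** Under Data analysis, the primary endpoint "will be evaluated using a conventional intention to treat analysis with logistic regression". The next sentence gives the exception: "if the observed intracluster correlation coefficient (ICC) is non-ignorable, we will use generalized estimating equations (GEE"). No cut-off, test or estimator for the ICC is given.

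Under Power and sample size, clustering is taken as present: "at an alpha =0.05, an ICC of 0.01, we require 1153 total patients to detect a clinically important difference with 80% power". The target is to "move the population from 40% achieving endpoint to at least 50% achieving endpoint". The cluster size and number of communities behind that figure are not stated.

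Under Setting, the project "RADAR involves collaboration with several First Nations communities in Alberta", and "approximately 1000 people with type-2 diabetes currently reside in the pilot communities". Under Implementation and evaluation, RADAR is introduced community by community and each community is described as its own control.

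**The concern.** The unit that receives RADAR is the community. The article's Discussion rejects randomising individual patients because the intervention's effects would spread within a health facility. That is also a reason to expect correlated outcomes within a community.

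The sample size section treats an ICC of 0.01 as large enough to raise the number of patients by about half. The analysis section treats patients as independent unless the trial's own data show otherwise. The two sections take different positions on the same quantity.

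The rule can fail because an ICC of this size is poorly estimated from a handful of communities. A true 0.01 can be judged ignorable, and the model that ignores it is then used for the primary test. Its standard error is too small, its interval too narrow, and its false-positive rate above 5%. In addition, the primary model is chosen after looking at the outcome data.

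**Working it through.** **Inputs from the article:** 40% against 50%, alpha 0.05, 80% power, ICC 0.01, 1153 patients before loss to follow-up (Power and sample size).

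**Assumed, because not stated:** two-sided test, 1:1 comparison, equal cluster sizes, number of communities.

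**1. Trying to reproduce 1153.** Without clustering, n per group = [1.96·√(2·0.45·0.55) + 0.8416·√(0.40·0.60 + 0.50·0.50)]² / 0.10² = 387.3. That rounds up to 388 per group, 776 in total. The figure 1153 cannot be reproduced from the stated inputs alone, because no cluster size is given. Back-solving:

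- design effect DE = 1153/776 = 1.486
- DE = 1 + (m − 1)·0.01, so m ≈ 49.6 patients per community
- 1153/49.6 ≈ 23 communities

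As a check, 776 × 1.49 = 1156, close to 1153. So the plan appears to add about 49% for clustering.

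**2. Type I error when the unadjusted test is used.** Error = 2·[1 − Φ(1.96/√DE)].

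- DE = 1.486: 2·[1 − Φ(1.608)] = 0.108
- continuity-corrected base of 816, DE = 1153/816 = 1.413: 0.099
- 1153 patients in 30 communities: 0.095; in 15: 0.139; in 10: 0.181; in 5: 0.28

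This formula applies to a comparison between clusters or against a fixed rate.

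**3. Type I error of the conditional rule.** This needs a cut-off, so several were tried by simulation: beta-binomial outcomes, ICC 0.01, true rate 40%, one result per patient, tested against a fixed 40%, ANOVA estimate of the ICC, 40,000 runs. After the switch, the GEE test uses an uncorrected sandwich variance; the figure in brackets uses a small-sample t correction.

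| Switch to GEE if | 23 × 50: unadjusted model kept | 23 × 50: error | 8 × 125: unadjusted model kept | 8 × 125: error |
|---|---|---|---|---|
| F test significant at 5% | 58% | 8.0% (7.5%) | 49% | 11.9% (10.3%) |
| ICC ≥ 0.01 | 54% | 7.7% (7.2%) | 57% | 12.9% (11.7%) |
| ICC ≥ 0.005 | 32% | 6.8% (5.8%) | 34% | 10.5% (7.8%) |
| ICC > 0 | 13% | 6.6% (5.1%) | 12% | 9.8% (5.2%) |
| Never (always logistic) | 100% | 11.1% | 100% | 19.8% |
| Always clustered | 0% | 7.1% (5.2%) | 0% | 11.2% (5.2%) |

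**4. If control and intervention data come from the same communities.** Simulated error of the unadjusted test (1153 patients, ICC 0.01, 20,000 runs per setting):

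| Contrast | 24 communities | 10 | 6 |
|---|---|---|---|
| Balanced pre-post, constant community effect | about 5% | about 5% | about 5% |
| Balanced pre-post, community effect varying by period | up to 8% | up to 12% | up to 16% |
| Five-step stepped wedge, no community terms | 6–7% | 7–10% | 9–15% |

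**The case against.** A reader might infer that the trial as planned runs at 11% type I error or more. The article does not support that. Eleven per cent is the error of the logistic test in trials where it is used. The plan switches to GEE in some trials, and at the implied cluster size the rule as a whole gives about 6.5–8%. Nor is 11% a floor: 30 communities or a continuity-corrected base gives slightly under 10%, and a balanced pre-post contrast with a stable community effect gives about 5%.

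One might also say that the cut-off and the GEE variance estimator belong in a statistical analysis plan, which is not shown. That stands. Their absence is not the point here, and the article nowhere says that the sandwich variance will be uncorrected; that is an assumption of the calculation. What does not fall away is the rule itself. Making an unadjusted test the default and adjustment conditional on the data is stated in the article, and a cut-off alone would not justify it. In the table, the rule holds roughly 5% only where the cut-off is so low that the clustered model is used in about 88% of trials and its variance is also corrected.

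The 8 × 125 setting can fairly be challenged. It matches the roughly 1000 patients mentioned under Setting, but not the cluster size implied by 1153: its design effect of 2.24 would require about 776 × 2.24 = 1738 patients. It shows what happens if the communities are few and large, and is not the plan's own design.

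Finally, each community is described as its own control, which can remove much of the community effect. Against that, Data analysis defines the endpoint as a change from baseline to the last recorded value in the intervention phase. That gives one result per patient, and the 40% usual-care rate comes from prior studies. The contrast is therefore not settled by the text, and both kinds are shown.

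**Conclusion.** The concern holds in this form: the stated rule lets the primary test ignore community clustering of the size for which the trial was planned, and it chooses the model by looking at the outcome data.

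At ICC 0.01, two-sided type I error is:

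- about 11% whenever the unadjusted model is used at the implied design effect of 1.49, and more with fewer, larger communities
- about 6.5–8% for the conditional rule with 23 communities of 50
- about 10–13% for the conditional rule with an assumed 8 communities of 125
- from about 5% to about 16% for the unadjusted test if the contrast is within community

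The rule-level figures assume one result per patient against a fixed rate, an uncorrected GEE variance, and a cut-off that the article does not give. The number of communities is unknown, so no single figure can be called the plan's error rate.

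**What to change.** Delete the condition. Specify in advance one primary model that accounts for community whatever the observed ICC: GEE with community as the cluster, or a mixed logistic model with a community random effect. Use a small-sample variance correction if the communities are few. In the simulations above, a clustered test with a t correction used in every trial gave 5.2% in both settings. Report the ICC with its interval as a description, not as a switch.

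The change is one sentence and uses standard software. Confidence intervals become wider than under the unadjusted model, by a factor of about √1.486 = 1.22 at the implied design effect. The 1153 patients already allow for that if communities average about 50 patients. With fewer, larger communities the allowance falls short: the same two-group calculation gives power of about 65% with 10 communities, against 80% with 24. That loss comes from the clustering and is not a reason to leave it out of the analysis.
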